### Percutaneous catheter ablation group

One hundred patients will be randomized to PCA and treated according to the protocol of the referring center. In all cases, complete PVI must be at least attempted and confirmed by bidirectional block. The referring investigator can then add any of the current methods of PeAF treatment, including substrate modification with the infusion of isoproterenol to uncover non-PVI triggers and CFAE. Lines can be drawn at the discretion of the investigators. Inducibility of AF at the end of the procedure will be recorded. Cardioversion will be allowed to restore SR.

After the 3-month blanking period, it will be left to the investigator’s preference to refer the patients with PeAF recurrence to a second PCA procedure, surgical ablation, or switch to a rate-control approach. The latter will be counted as a failed repeated procedure.

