**Methods/Design:**

This is a controlled (2:1) randomized trial comparing use of a percutaneous catheter with minimally invasive transthoracic surgical ablation of persistent atrial fibrillation. The inclusion and exclusion criteria, definitions, and treatment protocols are those reported by the 2012 Expert Consensus Statement on catheter and surgical ablation of atrial fibrillation. Patients will be randomized to either percutaneous catheter (*n* = 100) or surgical (*n* = 50) ablation as the first procedure. After 3 months, they are re-evaluated, according to the same guidelines, and receive a second procedure if necessary. Crossover will be allowed and data analyzed on an “intention-to-treat” basis. Primary outcomes are the incidence of sinus rhythm at 6 and 12 months and the proportions of patients requiring a second procedure.

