## Methods

The overall hypothesis of this study is that an initial surgical procedure has a higher probability of success than an initial percutaneous ablation, and therefore, fewer patients will be submitted to a second ablation. The proposed therapies are currently accepted and considered Class II indications in the current European Society of Cardiology [13] and European Association of Cardiothoracic Surgery [12] guidelines for the treatment of PeAf. As such, their comparison complies with the Declaration of Helsinki for the Ethical Principles of Medical Research in human subjects. The Ethics Committee of the University of Magna Grecia in Catanzaro (Italy) gave full approval to the study without conditions. No external financial support exists. Full reimbursement of the cost of the therapies has already been granted by the Italian National Health System.

All participants will be required to sign an informed consent to adhere to the study. The Surgical Staged Approach (SSA) strategy consists of an initial minimally invasive surgical ablation, followed by a percutaneous catheter ablation if necessary. To avoid any possible bias introduced by the difference in surgical techniques, we will use only the bipolar radiofrequency using the Estech cobra fusion ablator (Estech is a Market brand of Atricure Inc West Chester 45069 Ohio USA) introduced through a right minimal thoracotomy. The control group will receive the current standard strategy of PCA. In the case of recurrence of the AF, the second procedure will be either percutaneous or surgical. The inclusion criteria and the protocols for managing the pharmacologic and anticoagulant therapy, the description of the surgical approach, and the technique of the percutaneous ablation are those indicated by the 2012 HRS/EHRA/ECAS expert consensus statement on catheter and surgical ablation of AF [12] and the European Guidelines for the treatment of lone AF [13].

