### Staged surgical ablation group

Fifty patients will be randomized to surgical ablation of AF. The ablation procedure will be performed with the use of Estech cobra fusion, according to the manufacturer’s instructions and to the commonly described techniques [10,12,15]. Up to three applications will be allowed to ablate the left atrial box. Bidirectional block will be checked, and reasons for not obtaining it will be noted. Inducibility of AF at the end of the procedure will be recorded. Cardioversion will be allowed to restore SR. At the end of the procedure, the patient will be awakened and transferred to the ward. An interval of 3 months will be allowed after the initial ablation procedure, as per the Heart and Rhythm European Society Association/European Heart Rhythm Association/European Cardiac Arrhythmia Society expert consensus statement [13]. During this period, the recurrences of AF, atrial tachycardias, and atrial flutter will not be counted toward the primary or secondary end points. Antiarrhythmic medications may be continued for the first 3 months to avoid early recurrences. At 3 months, they must be stopped to assess recurrences. For patients continuing to have recurrence controlled by the therapy, it will be left to the preference of the investigator to continue the medical therapy or to refer the patient for a PCA.

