### Assessment of recurrence

The recurrence will be assessed by clinical follow-up at 1, 3, 6, 9, and 12 months with 12-lead ECG + 24 Holter monitoring. Transthoracic echocardiography will be also performed to record the presence of an atrial contraction in case of sinus rhythm. Quality of life will be assessed by a modified 36-item Short Form Health Survey and the Euro 5D questionnaire. The primary outcomes include the freedom from AF at 12 months, as detected by a 12-lead ECG and a 24-hour Holter examination after 3, 6, and 9 months of follow-up, and the occurrence of a second ablation procedure. The secondary outcomes include the duration of the procedures, freedom from any documented atrial arrhythmia, incidence of procedural complications, any late complication related to the procedures, and quality of life.

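### Second ablation is a primary outcome but also a discretionary treatment decision, while Table 1 is powered as if every recurrence were re-ablated; different referral between arms would bias the test

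*Protocol article*

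**What the plan says.** **Outcome.** The abstract (Methods/Design) states: "Primary outcomes are the incidence of sinus rhythm at 6 and 12 months and the proportions of patients requiring a second procedure". The section Assessment of recurrence lists as primary the freedom from AF at 12 months "and the occurrence of a second ablation procedure". Statistical analysis assigns the second-procedure proportions to a z test and an odds ratio, with significance at P < 0.05.

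**Who decides, catheter arm.** For recurrences of persistent AF after blanking, "it will be left to the investigator’s preference to refer the patients with PeAF recurrence to a second PCA procedure", to surgical ablation, or to rate control. Of rate control the section says: "The latter will be counted as a failed repeated procedure".

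**Who decides, surgical arm.** Discretion is stated only where drugs keep a recurrence in check; in that case "it will be left to the preference of the investigator to continue the medical therapy or to refer the patient for a PCA". No counting rule is attached to patients who stay on drugs.

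**Common criterion.** The abstract offers only this: "After 3 months, they are re-evaluated, according to the same guidelines, and receive a second procedure if necessary".

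**Hypothesis and planning.** Methods reasons that the first surgical procedure is more likely to succeed and that therefore "fewer patients will be submitted to a second ablation". Table 1 gives second-procedure fractions of 0.65, 0.55 and 0.50 (catheter) against 0.30 (surgical). Statistical analysis expects the number in sinus rhythm to be equivalent at the end and the second-procedure proportions to differ.

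**The concern.** A second ablation happens only if a patient recurs and someone then chooses to ablate again. The hypothesis concerns the first step, and the outcome records the product of both. Blinding is not mentioned, but the treating investigator can safely be assumed to know whether the first procedure was a thoracotomy or a catheter ablation. If recurrences are re-ablated less readily after surgery, for whatever clinical reason, the z test reads this as a benefit of surgery. No misconduct is needed.

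The other primary outcome would not expose the problem. Rhythm at 12 months is measured after any repeat procedure, and the plan expects it to be equivalent. The positive finding that the plan looks for is therefore the one that depends on referral.

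**Working it through.** **Inputs from the document.** 100 catheter and 50 surgical patients; first-procedure success 70% (surgical) and 35%, 45% or 50% (catheter, Table 1); P < 0.05. I assume a two-sided test. Referral fractions are also my assumptions, because the document gives none.

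**Step 1: reproduce the plan's power.** Pooled z test, with p̄ = (100·p_C + 50·p_S)/150, s0 = √[p̄(1−p̄)(1/100 + 1/50)], s1 = √[p_C(1−p_C)/100 + p_S(1−p_S)/50], and power = Φ[(|p_C − p_S| − 1.96·s0)/s1]. For 55% v 30% without success: p̄ = 0.467, s0 = 0.0864, s1 = 0.0817, so (0.25 − 0.1693)/0.0817 = 0.99 and power is 83.8%. The three columns give 98.8%, 83.8% and 65.1%, against 99%, 84% and 65% printed. Table 1 reproduces.

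**Step 2: what Table 1 assumes.** 1 − 0.35 = 0.65, 1 − 0.45 = 0.55, 1 − 0.50 = 0.50 and 1 − 0.70 = 0.30. These are exactly the tabulated second-procedure fractions, so referral is taken as 100% in both arms.

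**Step 3: allow for referral.** Second-procedure rate = recurrence r × referral q, by arm. The probabilities below come from exact enumeration of both binomials with the pooled z test. This method gives 85% for 55% v 30% and 99% for 65% v 30%, close to Table 1.

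*No difference in recurrence (r = 50% in both arms):*

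| Referral, catheter v surgical | Second procedures | Significant in favour of surgery |
|---|---|---|
| 90% v 90% | 45% v 45% | 2.7% |
| 90% v 80% | 45% v 40% | 8.8% |
| 90% v 70% | 45% v 35% | 22.1% |
| 90% v 60% | 45% v 30% | 43% |

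With full referral in both arms (50% v 50%) the figure is 2.8%.

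For scale, 50% recurrence among 50 surgical patients is 25 patients. Referral of 70% means that 7.5 of them, on average, stay on drugs.

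**Step 4: the rate-control rule, read two ways.**

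*Reading A: rate control is an event on this outcome.* Every catheter option listed for a recurrence then counts (q = 100%), while a surgical patient kept on drugs does not. With r = 50% in both arms, 80% surgical referral gives 50% v 40% and surgery significantly favoured in about 22% of trials; 70% gives 50% v 35% and 43%. Masking through the catheter arm is largely closed: true recurrence of 55% v 30% with 90% surgical referral gives 55% v 27% and 92% power.

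*Reading B: rate control is only a rhythm failure.* Bias can then also run the other way. Take referral of 70% (catheter) v 90% (surgical):
- Recurrence 55% v 30%: 0.55 × 0.70 = 38.5% v 0.30 × 0.90 = 27%. Power falls from 85% to 28%.
- Recurrence 65% v 30%: 45.5% v 27%. Power falls from 99% to 61%.

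Part of that loss comes from lower referral overall. Equal referral of 90% leaves 77% and 97% power respectively.

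**The case against.** **Discretion is not the same in the two arms.** A reader might infer that preference governs every recurrence in both. The document does not say so: in the surgical arm it is stated only for drug-controlled recurrence. The objection stands as a limit on how far surgical referral can fall. It does not remove the problem, because it makes the decision rule differ by arm.

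**A small referral gap need not settle the result.** A reader might infer that a modest difference can create or erase the primary finding. The figures do not support that in general. A 10-point gap gives 8.8% false significance at 50% recurrence. With 90% catheter referral, the expected counts reach P < 0.05 only at gaps of about 27 to 48 points (recurrence from 65% down to 30%). Erasing the planned 65% v 30% takes catheter referral of about 71% or less against full surgical referral, and only under reading B. Only the weakest scenario, 50% v 30%, is lost to a small gap, about 93% v 100%.

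**Other analyses look at rhythm.** Table 1 includes a comparison of sinus rhythm after the first procedure, and log-rank and Cox analyses are planned. These help, but none is named as primary and none is tied to the claim about second procedures.

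**This is a comparison of strategies.** Fewer procedures is a legitimate outcome for patients and payers, and operational triggers may sit in the cited guidelines or the full protocol. That is a fair reason to keep the outcome. But Methods derives fewer second ablations from better first-procedure success, and the article expressly leaves the decision to preference, so the outcome alone cannot test that reasoning.

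**Conclusion.** The concern holds in a bounded form. A primary outcome is a discretionary treatment decision, its scoring differs between arms, and its power calculation treats it as identical to recurrence. Under assumed gaps of 10 to 20 points, with equal 50% recurrence, false significance in favour of surgery rises from just under 3% to about 9% and 22%. If rate control is scored as an event in the catheter arm, 80% surgical referral alone reaches about 22%. Loss of power from a true difference arises only if rate control is not an event.

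These sizes rest on assumed referral fractions and a two-sided test. They show sensitivity and do not predict what investigators will do.

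**What to change.** 1. Reconcile the counting rules in the two intervention sections so that the same rule defines an event on this outcome in both arms. State whether rate control in the catheter arm, and continued drug therapy in the surgical arm, are events.
2. In Assessment of recurrence and Statistical analysis, prespecify a companion analysis in which every ECG- or Holter-documented recurrence after the 3-month blanking period of the first procedure is an event in both arms, whatever care follows.
3. Report by arm the fraction of documented recurrences that were re-ablated.
4. Claim a benefit of surgery on second procedures only if the two analyses agree.

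The choice of care stays with the investigator. The trial is already recruiting, so adding a companion analysis is easier to defend than replacing the primary outcome; it should be fixed before outcome data by arm are examined. The ECG and Holter recordings are already scheduled, so no extra patients or visits are needed. The cost is an amendment, a little more analysis and a somewhat harder-to-reach claim.

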### Statistical analysis

Randomization will be performed by using currently available computer software. Sample size is based on the hypothesis that the success rate of the first procedure will be approximately 70% for the surgical cases and 35% to 40% for the PCA cases. At the end of the interventions, the number of patients in SR should be equivalent in the two groups, whereas the proportions of those submitted to a second procedure, either percutaneous or surgical, should differ significantly. Variables will be analyzed with an intention-to-treat method. The three possible results of this study are described in Table 1. A flow chart depicting the most favorable result in which the power of the test is 98% is shown in Figure 1. Data will be expressed as mean ± SD and 95% confidence limits, as appropriate. Comparisons between patient groups will be performed with the Mann–Whitney test for continuous variables and the χ^2^ test for categoric variables. The *z* test and the odds ratio will be used for differences between proportions of patients receiving repeated procedures in the two groups. A value of *P* < 0.05 will be considered statistically significant. Time-to-event distributions will be estimated by the Kaplan-Meier method and compared with the log-rank test. The Cox proportional hazards model will be used to identify independent risk factors for recurrences. Stepwise selection procedure will be adopted. A value of *P* < 0.05 will be considered significant for variable entry for stepwise selection. Analyses are performed with the SPSS 18.0 software package (SPSS, Inc, Chicago, IL, USA).

**Table 1 T1:** Anticipated results for different success rates of first PCA procedure

**% of SR in the PCA group after first procedure**	**35%**	**45%**	**50%**
**χ**^ **2 ** ^**test for first procedure**	*P* < 0.0001	*P* = 0.007	*P* = 0.03
Power of the test	99%	84%	65%

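### A switch to rate control counts as a failed repeat procedure in the catheter arm only, so the second-procedure primary outcome may be counted by different rules in the two arms

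*Protocol article*

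**What the plan says.** **Catheter arm** (Methods, Percutaneous catheter ablation group). After the 3-month blanking period the investigator may "refer the patients with PeAF recurrence to a second PCA procedure, surgical ablation, or switch to a rate-control approach". On rate control the text adds: "The latter will be counted as a failed repeated procedure".

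**Surgical arm** (Methods, Staged surgical ablation group). On antiarrhythmic drugs the text says: "At 3 months, they must be stopped to assess recurrences". The next sentence begins "For patients continuing to have recurrence controlled by the therapy" and goes on: "it will be left to the preference of the investigator to continue the medical therapy or to refer the patient for a PCA". It does not say how a patient who stays on drugs is scored.

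**Outcomes** (Methods, Assessment of recurrence). "The primary outcomes include the freedom from AF at 12 months", "and the occurrence of a second ablation procedure".

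**Expectation** (Methods, Statistical analysis). Final sinus rhythm is expected to be equivalent in the two groups, while "the proportions of those submitted to a second procedure, either percutaneous or surgical, should differ significantly".

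**The concern.** The catheter-arm rule departs from the outcome definition, because rate control is not an ablation procedure. It is also one-sided. Read as part of the second-procedure count, it makes all three routes listed after catheter recurrence count. In the surgical arm, a patient with recurrence who is managed on drugs has no second ablation and, under the outcome as defined, no event. The numerators of the two proportions are then built differently.

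At stake is the primary outcome on which the trial expects to show a difference. In both arms the choice after recurrence is left to the investigator, so the share of patients not re-ablated need not be small or equal between arms. A difference in second procedures could then partly reflect the counting rule rather than recurrence.

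**Working it through.** **1. Reproduce the planned figures.** Inputs from Statistical analysis and Table 1: surgery n = 50, first-procedure success 70%; catheter n = 100, success 35%, 45% or 50%; P < 0.05, taken as two-sided. Pooled-variance formula:

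power = Φ[(d − 1.96·SE0)/SE1], with SE0 = √(p̄(1−p̄)(1/50+1/100)) and SE1 = √(0.70·0.30/50 + p(1−p)/100).

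- p = 0.35: d = 0.35, SE0 = 0.0864, SE1 = 0.0805, power 98.8% (Table 1: 99%)
- p = 0.45: d = 0.25, SE0 = 0.0864, SE1 = 0.0817, power 83.8% (84%)
- p = 0.50: d = 0.20, SE0 = 0.0858, SE1 = 0.0819, power 65.1% (65%)

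The table reproduces.

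**2. What planning assumes about second procedures.** Table 1 gives fractions of 0.65, 0.55 and 0.50 against 0.30. These are 1 − 0.35, 1 − 0.45, 1 − 0.50 and 1 − 0.70. Planning therefore treats every first-procedure failure, in either arm, as a second procedure.

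**3. What the Methods text delivers.**

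| After recurrence, managed by | Catheter arm | Surgical arm |
|---|---|---|
| Second ablation | event | event |
| Rate control | counted as a failed repeat procedure | no rule |
| Continued drugs | no rule | allowed, no counting rule; no event under the outcome definition |

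**4. Effect on the test if the catheter rule enters the count.** Let r be the true recurrence rate, equal in both arms, and f the share of surgical recurrences kept on drugs. The documents give no value for f, so a range is shown. The catheter arm is counted at r and the surgical arm at r(1 − f), so the expected difference is r·f in favour of surgery. For r = 50% and f = 20% that is 50% against 40%.

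The test is z = (x_c/100 − x_s/50)/√(p̄(1−p̄)(1/100+1/50)), with p̄ = (x_c + x_s)/150, rejecting when |z| > 1.96. This is equivalent to the uncorrected χ² test. Summing the exact binomial probabilities over all rejecting pairs gives the two-sided rejection rate:

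| True recurrence r | f = 0 | f = 10% | f = 20% | f = 30% |
|---|---|---|---|---|
| 30% | 5.1% | 6.5% | 11.6% | 21.2% |
| 50% | 5.6% | 9.8% | 22.5% | 43.2% |
| 65% | 5.0% | 12.4% | 34.3% | 63.9% |

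The rows at 30% and 65% are the protocol's own surgical failure rate and its highest catheter failure rate. Almost all the excess favours surgery: at r = 30%, f = 20%, 11.3% of the 11.6% does so.

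**The case against.** The best counter-argument is that the catheter-arm sentence need not touch the second-procedure count. It can be read as saying that a rate-controlled patient is a failure of the repeat-ablation strategy on final rhythm. The outcome is defined as a second ablation, which such a patient never has. On that reading the computed bias disappears. This stands as a possible reading, but the words refer to a repeated procedure, and the text does not say which outcome the rule feeds.

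Three further objections stand in part:

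- **The two states are not the same.** Rate control accepts AF, whereas the surgical-arm option concerns recurrence controlled by therapy. The like-for-like cases are rate control after surgery and drug-controlled recurrence after catheter ablation. The article gives a rule for neither, so the case for a common rule remains.
- **The article is a condensed text.** Fine scoring detail may sit in a fuller document, and silence alone would be no finding. Here, however, a rule is stated for one arm and conflicts with the stated outcome.
- **The size is conditional.** Nothing excludes continued drugs after catheter ablation. If a share f_c of catheter recurrences also went uncounted, the expected difference would fall to r(f − f_c).

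A reader might infer that the documents score continued drugs after surgery as nothing. They do not say so; no event follows only from the outcome definition, and a post-blanking recurrence on ECG or Holter could still count against freedom from AF. A reader might also infer that both primary outcomes are biased towards surgery. No difference between arms in scoring 12-month freedom from AF is documented: a rate-controlled patient in AF fails there anyway, and no text scores catheter patients on drugs as failures. Nor is the second-procedure outcome the sole basis of the sample size; that rests on first-procedure success, from which Table 1 derives the second-procedure fractions.

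**Conclusion.** The point holds in a limited form. A one-sided counting rule conflicts with the definition of a primary outcome and has no counterpart in the surgical arm. If the rule enters the second-procedure count, that outcome is tilted towards surgery by r·f. With equal true recurrence, the two-sided rejection rate rises from about 5% to between 6.5% and 64% over the range examined.

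Those figures rest on four assumptions: the rule feeds the second-procedure count; every catheter recurrence is counted; 10% to 30% of surgical recurrences are kept on drugs; and the test is two-sided without continuity correction. With f = 0 there is no bias. The documents therefore do not establish that the comparison will favour surgery, only that the counting rule permits it.

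**What to change.** State one scoring rule for both arms. Either of these would do:

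- Count only second ablations actually performed, and report rate control as a rhythm failure in both arms.
- Count every post-blanking recurrence alike in both arms, whether managed by re-ablation, drugs or rate control. This matches the planning in Table 1, but the outcome should then be renamed, since it is no longer a count of ablations.

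In either case, say how sinus rhythm maintained on drugs is scored at 12 months, identically in both arms. Separately, the sponsor should reconcile the surgical-arm sentences on stopping and on continuing drugs at 3 months. They can be read in sequence, but continuing fits poorly with having stopped. No clinical rule is proposed here.

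The cost is one paragraph in the outcome definition, with no new data and no change in care. The apparent advantage of surgery may shrink. The first option also costs power if some recurrences in both arms are not re-ablated. For fractions of 0.65 against 0.30, with an equal 10%, 20% or 30% not re-ablated in each arm, the formula in step 1 applied to the reduced fractions gives 97%, 92% and 86%, compared with 99% in Table 1.

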**Difference between proportions**			
Fraction of second procedures in the two groups	0.65-0.30	0.55-0.30	0.50-0.30
Difference between fractions	0.35	0.25	0.2
95% confidence interval of difference	0.1 to 0.5	0.1 to 0.4	0.0 to 0.3

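### A recurrence that is not re-ablated has a counting rule in the catheter arm only, although second procedures are a primary outcome

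*Protocol article*

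**What the plan says.** **Catheter arm** (Methods, Percutaneous catheter ablation group). After the 3-month blanking period the investigator may choose to "refer the patients with PeAF recurrence to a second PCA procedure, surgical ablation, or switch to a rate-control approach". The rate-control option then gets a counting rule: "The latter will be counted as a failed repeated procedure". Continued antiarrhythmic drugs are not listed as an option.

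**Surgical arm** (Methods, Staged surgical ablation group). Drugs are stopped at 3 months so that recurrence can be assessed. For patients whose recurrence is controlled by drugs, "it will be left to the preference of the investigator to continue the medical therapy or to refer the patient for a PCA". No counting rule follows, and rate control is not listed.

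**Outcome.** Assessment of recurrence names as primary outcomes freedom from AF at 12 months "and the occurrence of a second ablation procedure". Statistical analysis expects sinus rhythm to be equivalent at the end, while "the proportions of those submitted to a second procedure, either percutaneous or surgical, should differ significantly", and assigns a z test and odds ratio to that comparison.

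**Planning figures.** The Table 1 row "Fraction of second procedures in the two groups" gives 0.65, 0.55 or 0.50 for catheter against 0.30 for surgery.

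**Common provisions.** The abstract says that after 3 months patients in both arms are evaluated again: "they are re-evaluated, according to the same guidelines, and receive a second procedure if necessary". The ECG and Holter schedule is also the same in both arms.

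**The concern.** Both arms leave the management of a recurrence to the investigator, and both offer a route without a second ablation. Only the catheter arm's route has a rule, and that rule treats a patient who had no repeat procedure as having had a failed one. The article does not say whether this classification feeds the second-procedure outcome, the rhythm outcome, or both.

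The second-procedure proportion is where the trial expects its difference. If the catheter rule enters that count and surgical patients kept on drugs are left out, the comparison favours surgery even when both first procedures fail equally often. The common visit schedule and the common re-evaluation at 3 months govern how recurrence is detected and reviewed, not how it is counted. Intention-to-treat fixes the arm in which a patient is analysed, not whether an event occurred.

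**Working it through.** **Inputs.** From the article: 100 catheter and 50 surgical patients; significance at P < 0.05; the Table 1 fractions. Assumed: a two-sided test (sidedness is not stated, but two-sided reproduces Table 1), and the share of recurrences not re-ablated, for which the documents give no figure.

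**Formula.** With counted fractions p1 (catheter, n1 = 100) and p2 (surgery, n2 = 50), pooled fraction p = (100·p1 + 50·p2)/150, SE0 = √[p(1−p)(1/100 + 1/50)] and SE1 = √[p1(1−p1)/100 + p2(1−p2)/50]:

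P(significant in favour of surgery) = Φ[(p1 − p2 − 1.96·SE0)/SE1].

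**Step 1: reproduce Table 1.** For 0.65 vs 0.30: p = 0.533, SE0 = 0.0864, SE1 = 0.0805, so Φ[(0.35 − 0.1694)/0.0805] = Φ(2.24) = 98.8%. For 0.55 and 0.50 vs 0.30 the results are 83.8% and 65.1%. Table 1 states 99%, 84% and 65%.

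**Step 2: what Table 1 assumed.** The catheter fractions 0.65, 0.55 and 0.50 are 1 − 0.35, 1 − 0.45 and 1 − 0.50; the surgical fraction 0.30 is 1 − 0.70. The planned second-procedure fraction therefore equals first-procedure failure in each arm.

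**Step 3: the rule in one arm only, with equal efficacy.** Let true recurrence be R in both arms. All catheter recurrences count (p1 = R). A share d of surgical recurrences is kept on drugs and not counted (p2 = R(1 − d)).

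| d (assumed) | R = 30%: counted | Chance for surgery | R = 50%: counted | Chance for surgery |
|---|---|---|---|---|
| 0 | 30% vs 30% | 2.5% | 50% vs 50% | 2.5% |
| 10% | 30% vs 27% | 5.5% | 50% vs 45% | 8% |
| 20% | 30% vs 24% | 11% | 50% vs 40% | 21% |
| 30% | 30% vs 21% | 21% | 50% vs 35% | 41% |
| 40% | 30% vs 18% | 34% | 50% vs 30% | 65% |

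Example for R = 30%, d = 20%: p = 0.28, SE0 = 0.0778, SE1 = 0.0758, so Φ[(0.06 − 0.1524)/0.0758] = Φ(−1.22) = 11%. Exact binomial calculations agree closely (5.5% to 35% at R = 30%; 9% to 67% at R = 50%).

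**Step 4: one rule in both arms.** Count only performed second ablations, and let the same share q of recurrences go without re-ablation in each arm. With equal recurrence, p1 = p2 and the chance of a false result for surgery stays at 2.5%. Under the plan's 65% vs 30%:

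| q (assumed) | Counted | Power |
|---|---|---|
| 0 | 65% vs 30% | 98.8% |
| 10% | 58.5% vs 27% | 97% |
| 20% | 52% vs 24% | 92% |
| 30% | 45.5% vs 21% | 86% |

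**The case against.** The surgical arm has a silence, not a contrary rule. A reader might infer that the article excludes drug-managed surgical recurrences from the count; it does not say so, and a full protocol or analysis plan may settle it. That stands. It does not remove the point, because the article itself fixes a rule for one arm of a primary comparison.

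The two groups are not clinically alike. Drug-controlled recurrence after surgery is a partial success of rhythm control, while rate control gives rhythm control up, and other surgical failures go to catheter ablation if necessary. This also stands, and it limits how many surgical patients could be affected. But both are recurrences without re-ablation, and rate control after surgery has no rule at all.

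The larger percentages are conditional. They need the catheter rule to enter the second-procedure count, surgical patients on drugs to be left out, and assumed shares. The 65% figure also needs 50% surgical failure, against the planned 30%, and 40% of those patients kept on drugs. Its match with the 65% in Table 1 follows from choosing 40%. Freedom from AF is less exposed, since it is assessed on the same schedule in both arms.

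A reader might also infer that, if the catheter rule stays out of the count, only catheter patients drop out and power collapses. The documents do not support this. On that reading the outcome is ablations performed in both arms, so surgical patients on drugs drop out as well, and the loss with equal shares is the moderate one in Step 4.

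Finally, Table 1 may simply assume that every failure is re-ablated. It does not prove that the trial means to count every recurrence.

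**Conclusion.** The point holds as an unequal and incomplete counting rule on a primary outcome. If the catheter-arm rule enters the second-procedure outcome, and surgical recurrences kept on drugs do not, the comparison is biased towards surgery. At the planned surgical recurrence of 30%, applied to both arms, the chance of a significant result for surgery rises from 2.5% to between 5.5% and 34% for assumed shares of 10% to 40% kept on drugs; at 50% recurrence it rises to between 8% and 65%. At small shares the effect is modest. The direction follows from the rule so applied; the size rests on shares that the documents do not give.

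Two stronger conclusions do not follow: that the protocol states opposite rules for the two arms, and that first-procedure failure must replace the second procedure as the primary outcome. The Discussion gives fewer invasive procedures as an aim of the staged approach, so performed ablations are a legitimate outcome once they are counted alike. The plan should be changed on this point, before outcomes are compared.

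**What to change.** In the two arm-specific sections of Methods, list the same options after a recurrence beyond the blanking period: second ablation (catheter or surgical, as each arm allows), continued antiarrhythmic drugs, or rate control. Then state one rule for both arms:

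- The second-procedure outcome counts only second ablations actually performed.
- Rate control or continued antiarrhythmic drugs for a recurrence after blanking counts as failure of the first procedure, in either arm.
- First-procedure failure is reported by arm next to the second-procedure outcome. It is the quantity that the Table 1 fractions equal, and it shows whether a difference in ablations performed reflects efficacy or the choice of management.

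The change is one of wording and needs no extra visits. It has two costs. Power for performed ablations falls below Table 1's 99%, to about 97%, 92% or 86% if 10%, 20% or 30% of recurrences in both arms are not re-ablated (assumed shares). And because the trial is already recruiting, patients already managed after a recurrence must be reclassified from existing records.
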